### Inclusion criteria

All patients who undergo a laparoscopic cholecystectomy, either as an emergency or elective procedure, at each of the hospital campuses are eligible for inclusion in this study. There is no gold standard approach for chemical and mechanical thromboprophylaxis, and the proposed intervention is one of the accepted surgical techniques for the prevention of VTE. All of the involved hospitals had already adopted SCCDs alone prior to the commencement of this study.

### Exclusion criteria

Participants will be excluded based on the following criteria:
If they are fitted with GCSs exclusively, combined GCSs and SCCDs, or if no mechanical prophylaxis is used intra-operatively.A planned or unplanned conversion to open cholecystectomy.Under the age of 18 years.

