### Primary outcomes

The primary outcome is the incidence of symptomatic VTE by day 30 post-operatively, which is proven by any imaging technique.

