### Secondary outcomes

The secondary outcome is the incidence of surgical bleeding, particularly bleeding that is defined as a major bleeding event, characterized by the need for radiological or surgical control, a blood transfusion, or a drop in the baseline hemoglobin of >20 g/L.

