### Study method

All patients requiring either an elective or an emergency laparoscopic cholecystectomy will be recruited for this study.

For those participants who are booked for an elective laparoscopic cholecystectomy, they will be admitted to the hospital on the day of their surgery. A sequential calf compressor device will be fitted as per the manufacturer’s specifications immediately prior to the commencement of surgery, and will be used for the duration of surgery. At the completion of surgery and immediately before the patient is transferred to the post-anesthetic care unit, the SCCDs will be removed. Chemical thromboprophylaxis will be initiated by the subcutaneous injection of 40 mg of enoxaparin, 5000 IU of dalteparin, or 5000 IU of heparin at any time at the discretion of the treating team. Subsequent doses of enoxaparin and dalteparin (if required) are given 24 hours later following the initial dose. No participant undergoing an elective operation is to have GCSs fitted either pre- or post-operatively. Participants may be discharged home on the day of their surgery at the discretion of their treating surgeon. During the operation, positioning of the patient and the intra-abdominal insufflation pressure will be at the discretion of the treating surgeon.

For those participants who are undergoing an emergency laparoscopic cholecystectomy, access to the theater may differ across the various hospital campuses. This will be controlled for by the acquisition of data pertaining to the length of time of admission to the hospital relative to the timing of their actual surgery. For these patients, it is anticipated that they will have received chemical thromboprophylaxis prior to their operation. This data will be collected and analyzed separately as a sub-analysis. There will be no restrictions on the type or timing of chemical thromboprophylaxis used.

Demographic and operative data will be collected at the end of the operation by the surgical fellow/registrar/resident who has been recruited to the study and trained under the auspices of the registrar collaborative. This process will also be supervised by the PI from each institution.

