### Limitations/risk of bias

The cohort design of the study limits selection and participation bias. It is not expected that the measurements of primary or secondary outcomes will pose a high risk of bias, as these outcomes are measured objectively by biochemical and radiological parameters. However, abnormal blood results, such as decreased hemoglobin count, can result from a poor blood sample or dilutional effects.

Limitations of the study include the use of a historical control, although this is partially addressed by including the same and similar hospitals between studies. Utilizing a collaborative authorship model has great advantages but also presents limitations, such as the potential for inconsistent data entry. The main limitation in terms of VTE risk is the variation in hospital policy regarding the use of chemical VTE thromboprophylaxis; however, restricting the study to hospitals with identical chemical prophylaxis policies would exclude most sites, and requiring individual participant consent and recruitment was deemed too resource-intensive and likely to introduce bias. Additionally, there was no patient or public involvement in the design of the study.

The use of a single type of operation, laparoscopic cholecystectomy, limits the heterogeneity of the operative data and, therefore, potential bias. However, the incidence of VTE in laparoscopic cholecystectomy is lower than that for other higher-risk operations (e.g., abdominal cancer resections), necessitating a large population. While abdominal laparoscopy is considered high risk for VTE, it is clearly not the highest-risk surgery. Results of this study may not be transferable to higher-risk operations but may inform and alleviate safety concerns for a future study on this population.

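### Excluding unplanned conversions to open surgery removes patients after exposure has begun and biases the bleeding incidence downwards; the effect on VTE is probably in the same direction but smaller

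*Protocol article*

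**What the plan says.** All references are to the protocol article.

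- **Exclusion criteria:** patients are excluded for "A planned or unplanned conversion to open cholecystectomy".
- **Inclusion criteria:** the eligible population is given as "All patients who undergo a laparoscopic cholecystectomy, either as an emergency or elective procedure, at each of the hospital campuses are eligible for inclusion". The Study population section is equally broad.
- **Study method, recruitment:** "All patients requiring either an elective or an emergency laparoscopic cholecystectomy will be recruited for this study".
- **Study method, exposure (described for elective patients):** the device is fitted "immediately prior to the commencement of surgery, and will be used for the duration of surgery".
- **Study method, data capture:** "Demographic and operative data will be collected at the end of the operation". By then it is known whether the operation was converted.
- **Primary outcomes:** "The primary outcome is the incidence of symptomatic VTE by day 30 post-operatively, which is proven by any imaging technique".
- **Secondary outcomes:** a major bleed is "characterized by the need for radiological or surgical control, a blood transfusion" or a haemoglobin drop of more than 20 g/L.
- **Aims and objectives:** the incidence of surgical bleeding is part of the second of two main objectives.

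The article gives no conversion rate and no bleeding rate. It describes no separate follow-up or reporting of converted patients. The Limitations/risk of bias section does not mention the exclusion.

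**The concern.** A planned open operation is known before the device is fitted, and excluding it simply defines the population. An unplanned conversion is different. It occurs during the operation, after exposure has started, and one possible reason for it is bleeding that cannot be controlled laparoscopically. Excluding on it makes membership of the cohort depend on an event that can be part of the outcome.

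Three things are at stake:

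- **Bleeding.** The reported incidence omits bleeds that led to conversion. Statistical analysis then restores nothing, because by rule these patients are not in the cohort. The planned multivariable model for bleeding would be fitted to the same truncated cohort.
- **VTE.** If converted patients have a higher risk than completed laparoscopic cases, the observed rate is lower than the rate for everyone who started the operation with the device. In a non-inferiority assessment against a fixed ceiling, that error is in the lenient direction.
- **Applicability.** Whoever chooses the prophylaxis does not yet know whether the operation will be converted. A rate for completed laparoscopic cases alone does not answer the question for all patients who require the operation.

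**Working it through.** **1. The plan's own figure.** From Study population: assumed rate p1 = 0.24%, ceiling p0 = 0.45%, one-sided alpha 0.05, power 0.8. The one-sample normal approximation is

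n = {[z(0.95)·√(p0(1−p0)) + z(0.80)·√(p1(1−p1))] / (p0−p1)}² = {[1.645·0.06693 + 0.8416·0.04893] / 0.0021}² = 5189.

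The stated 5190 is reproduced, so this point does not rest on an arithmetic error in the plan.

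**2. The pass limit in events.** Expected events at 0.24%: 5190 × 0.0024 = 12.5. An exact one-sided 5% binomial test against 0.45% passes with at most 15 events: P(≤15 | 0.45%) = 0.045, while 16 events would give 0.072. P(≤15 | 0.24%) = 0.81. The gap between expectation and limit is 2–3 events.

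**3. Bleeding: direction.** The definition does not confine surgical control to a return to theatre, and transfusion or a haemoglobin drop also qualifies. A patient converted because of bleeding can therefore meet the outcome and the exclusion at once. Removing such patients lowers the rate whenever major bleeding is more frequent among converted than among completed cases.

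**4. Bleeding: illustrative size.** Let c be the share converted, b the major bleeding rate if converted, and 1.5% the rate otherwise. All three are assumptions; none is in the document.

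True rate = (1−c)·1.5% + c·b; reported rate = 1.5%; understatement = 1 − 1.5%/true rate.

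| c | b | True rate | Understatement |
|---|---|---|---|
| 2% | 20% | 1.87% | 20% |
| 2% | 30% | 2.07% | 28% |
| 3% | 20% | 2.06% | 27% |
| 3% | 30% | 2.36% | 36% |

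These inputs imply a bleeding risk ratio of 13–20 (20/1.5 to 30/1.5). With a ratio of 10, the understatement 1 − 1/(1−c+c·RR) is 8% at c = 1%, 15% at c = 2% and 31% at c = 5%.

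**5. VTE: net events lost.** The sample is fixed at 5190, so each excluded patient is replaced by a completed laparoscopic case carrying the ordinary 0.24% risk. The bias in the count is therefore the excess only:

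net events lost = 5190 · c · 0.0024 · (RR−1).

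Here c and RR are again assumptions. The last column is P(≤15 events) if the full-cohort rate 0.24%·(1−c+c·RR) applied, to be compared with 0.81.

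| c | RR | Net events lost | Full-cohort rate | Chance of passing |
|---|---|---|---|---|
| 2% | 2 | 0.25 | 0.245% | 0.79 |
| 2% | 4 | 0.75 | 0.254% | 0.75 |
| 3% | 2 | 0.37 | 0.247% | 0.78 |
| 3% | 4 | 1.1 | 0.262% | 0.71 |
| 5% | 2 | 0.62 | 0.252% | 0.76 |
| 5% | 4 | 1.9 | 0.276% | 0.64 |

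At RR = 1 there is no bias.

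**The case against.** **The size is assumed throughout.** This stands. The article gives no conversion rate, no bleeding rate and no reasons for conversion. A bleeding risk ratio of 13–20 is high, and a ratio of 10 gives 15% understatement at 2% conversion. Only the direction for bleeding can be argued from the document, through its outcome definition.

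**Excluding conversions may be the like-for-like choice for VTE.** This also stands. The primary comparison is with a published rate, and the article does not say whether that cohort excluded conversions. If it did, an analysis of completed laparoscopic operations is the fairer comparison. This supports reporting VTE both ways. It does not help the bleeding outcome, for which the article states no margin or reference rate.

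**The article has a reason to standardise the operation.** The Abstract and Limitations argue for a single procedure to reduce heterogeneity, and completed laparoscopic cholecystectomy is a definable population. But it is not the population stated in Study population, Inclusion criteria and Study method.

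**The Limitations section might seem to deny the problem.** It says: "The cohort design of the study limits selection and participation bias". A reader might infer a claim that excluding conversions causes no selection bias. Read with Study design and the rest of Limitations, the sentence concerns avoiding individual recruitment and consent. The most that can be said is that the exclusion is not listed as a limitation.

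**The outcome affected most is secondary.** True, although bleeding incidence also belongs to one of the two main objectives.

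**Conclusion.** The point holds for bleeding. As written, the rule removes patients on an intra-operative event that can itself be a major bleed, so the reported incidence is biased downwards and does not describe the stated population. The size cannot be derived from the document. Under the assumptions shown (2–3% conversion; 20–30% major bleeding if converted, 1.5% otherwise), a true rate of 1.9–2.4% would be reported as 1.5%.

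For VTE the bias is probably downward, provided converted patients carry a higher risk, but it is smaller: about 0.25–1.1 events net at 2–3% conversion and a risk ratio of 2–4, and up to 1.9 at 5%.

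A reader might infer that the exclusion tilts the primary non-inferiority result decisively towards passing. The documents do not support that. The net loss is below the 2–3 event gap throughout the ranges shown, neither the conversion share nor the risk ratio is given, and the reference cohort's handling of conversions is not stated. Counting every VTE event among converted patients as lost would also overstate the effect, because their replacements carry the baseline risk.

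**What to change.** In the Exclusion criteria, delete the words *or unplanned*, so that only planned open operations stay excluded. Then:

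- follow up every operation started laparoscopically with the compression device alone;
- include converted patients in the bleeding analysis;
- report VTE both with and without conversions, keeping the completed-laparoscopic analysis available for comparability with the reference study;
- report the number of conversions, so that readers can judge the influence.

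The cost is small. Operative data are already collected at the end of surgery, and a telephone call between days 30 and 35 is already planned for all patients. The change adds a few per cent more calls and slightly more heterogeneity. It alters who is analysed, not how patients are treated. It belongs in the protocol because patients who are never followed cannot be recovered at analysis.

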### Primary outcomes

The primary outcome is the incidence of symptomatic VTE by day 30 post-operatively, which is proven by any imaging technique.

### Secondary outcomes

The secondary outcome is the incidence of surgical bleeding, particularly bleeding that is defined as a major bleeding event, characterized by the need for radiological or surgical control, a blood transfusion, or a drop in the baseline hemoglobin of >20 g/L.

### Study method

All patients requiring either an elective or an emergency laparoscopic cholecystectomy will be recruited for this study.

For those participants who are booked for an elective laparoscopic cholecystectomy, they will be admitted to the hospital on the day of their surgery. A sequential calf compressor device will be fitted as per the manufacturer’s specifications immediately prior to the commencement of surgery, and will be used for the duration of surgery. At the completion of surgery and immediately before the patient is transferred to the post-anesthetic care unit, the SCCDs will be removed. Chemical thromboprophylaxis will be initiated by the subcutaneous injection of 40 mg of enoxaparin, 5000 IU of dalteparin, or 5000 IU of heparin at any time at the discretion of the treating team. Subsequent doses of enoxaparin and dalteparin (if required) are given 24 hours later following the initial dose. No participant undergoing an elective operation is to have GCSs fitted either pre- or post-operatively. Participants may be discharged home on the day of their surgery at the discretion of their treating surgeon. During the operation, positioning of the patient and the intra-abdominal insufflation pressure will be at the discretion of the treating surgeon.

For those participants who are undergoing an emergency laparoscopic cholecystectomy, access to the theater may differ across the various hospital campuses. This will be controlled for by the acquisition of data pertaining to the length of time of admission to the hospital relative to the timing of their actual surgery. For these patients, it is anticipated that they will have received chemical thromboprophylaxis prior to their operation. This data will be collected and analyzed separately as a sub-analysis. There will be no restrictions on the type or timing of chemical thromboprophylaxis used.

Demographic and operative data will be collected at the end of the operation by the surgical fellow/registrar/resident who has been recruited to the study and trained under the auspices of the registrar collaborative. This process will also be supervised by the PI from each institution.

As part of this study, all patients will be contacted between days 30 and 35 post-operatively via telephone to inquire about symptoms that may be suggestive of the development of VTE, irrespective of the clinical follow-up. At this time, verbal consent will be obtained to proceed with a pro forma telephone questionnaire, and this process will occupy approximately 2–5 minutes of their time. For those participants who have symptoms suggestive of a VTE based on the Wells criteria[14], they will be invited back to their treating hospital for image confirmation of VTE, and if this is confirmed, then an anticoagulation regimen will be commenced at the discretion of the clinical team, the duration of which is guided by the latest guidelines from the Thrombosis and Haemostasis Society of Australia and New Zealand[1].

### Data collection

All data will be transcribed into a central REDCap database, accessible electronically and maintained at the lead hospital^[^15,16^]^. The defined time point for data collection will be between days 30 and 35 post-operatively, through a telephone consultation using a proforma with specific questions (Box 1) to determine if a participant has symptomatic VTE present. If the participant’s symptoms are suggestive of a VTE, they will be invited back to the treating hospital to confirm this via imaging techniques. The database will be regularly checked for completeness, and data will be randomly audited for fidelity issues.

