## Methods and analysis

### Aims and objectives

This study aims to determine if a standardized approach to the intra-operative use of SCCDs only will result in a non-inferior incidence of 30-day symptomatic VTE in patients undergoing either elective or emergency laparoscopic cholecystectomies compared to a reference previously published combined mechanical prophylaxis comparator group from the same mix of centers[12].

There are two main objectives of this prospective point prevalence study:
To determine whether the structured approach of VTE prophylaxis using SCCDs alone is non-inferior with respect to the incidence of symptomatic VTE by day 30 post-operatively when compared to the historical control.To determine the incidence of surgical bleeding and SCCD-related complications.

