## Ethics and dissemination

This study will be conducted in full conformance with the principles of the “Declaration of Helsinki,” Good Clinical Practice, and within the laws and regulations of the states of Victoria, New South Wales, and South Australia. The study was approved by a local ethics committee (LRR 094/21) and registered with the Australian Clinical Trials Network (*ACTN number blinded*), where a full copy of the protocol is also stored.

Data will initially be obtained in a re-identifiable manner (hospital and UR number are recorded). This is required to enter the 30-day survey and audit of the 30-day morbidity into the patient dataset. This will also ensure data completeness by requesting missing data from the person involved in inputting that particular participant’s data into the database, and by allowing six-monthly random data checks to ensure accuracy. These data will be marked as identifiers in REDCap, and only aggregate, de-identified data will be extracted for analysis. Electronic data will be destroyed by electronic shredding seven years after publication.

The final publication will be written according to the STROCSS guidelines[19]. Dissemination will occur through participating hospitals, as well as publicly through local, national, and international conferences, and through peer-reviewed journals.

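### The outcome is VTE from surgery to day 30, but the day 30–35 call is described as checking for VTE present at the call; state the look-back period and the cut-off

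*Protocol article*

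**What the plan says.** All references are to the Protocol article.

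- **Primary outcomes:** "The primary outcome is the incidence of symptomatic VTE by day 30 post-operatively, which is proven by any imaging technique". This is a count of events accumulated from surgery to day 30.
- **Aims and objectives:** "There are two main objectives of this prospective point prevalence study". Study design repeats the point-prevalence label.
- **Data collection:** "The defined time point for data collection will be between days 30 and 35 post-operatively", carried out "through a telephone consultation using a proforma with specific questions (Box 1) to determine if a participant has symptomatic VTE present".
- **Study method:** the same call is "to inquire about symptoms that may be suggestive of the development of VTE, irrespective of the clinical follow-up". Participants whose symptoms suggest VTE on the Wells criteria then go to confirmation: "they will be invited back to their treating hospital for image confirmation of VTE". If VTE is confirmed, anticoagulation is started at that point.
- **Ethics and dissemination:** identifiers are kept for a stated reason: "This is required to enter the 30-day survey and audit of the 30-day morbidity into the patient dataset". This is the only mention of a 30-day audit.
- **Study population:** 5190 patients; one-sided test of an assumed 0.24% against 0.45%; alpha 0.05; power 0.8.

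**The concern.** The outcome covers a period, while the call is described as a check at one moment after that period has closed. Read literally, the two give different counts for two kinds of patient.

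1. **Early event treated elsewhere.** A deep vein thrombosis is imaged and treated on day 8 at a hospital outside the study, and the patient has no symptoms on day 32. This is an event under the outcome definition. A call that looks for VTE now present need not find it. The pathway in Study method (symptoms, then imaging, then start of treatment) has no branch for a patient already diagnosed.
2. **Late event.** Symptoms begin on day 33, the call is on day 35 and imaging follows. This is not an event by day 30, but the pathway would find and confirm it. The article does not say which date decides.

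The first error lowers the observed rate and so favours a finding of non-inferiority. The second raises it and costs power. Both matter because few events are expected.

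**Working it through.** **Step 1. Reproduce the plan's figure.** Inputs from Study population: p0 = 0.0045, p1 = 0.0024, one-sided alpha 0.05, power 0.80. The one-sample score formula is

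n = [(z₀.₉₅ √(p0(1−p0)) + z₀.₈₀ √(p1(1−p1))) / (p0 − p1)]²

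= [(0.11009 + 0.04118) / 0.0021]² = 5189.002, which rounds up to 5190. The stated sample size is reproduced, and nothing below changes it.

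**Step 2. Find how many events decide the result.** Expected events at n = 5190:

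- at 0.24%: 5190 × 0.0024 = 12.5
- at 0.45%: 5190 × 0.0045 = 23.4

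The article does not give a critical count. An exact binomial test at one-sided 5% is used here as the working rule:

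- P(X ≤ 15 | 0.45%) = 0.045
- P(X ≤ 16 | 0.45%) = 0.072

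The test therefore passes with 15 events or fewer. Power at 0.24% is P(X ≤ 15) = 0.81.

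**Step 3. Missed early events (illustration).** Let m be the share of true events not ascertained. The documents give no value, so a range is assumed. The chance of passing at a true 0.45% is P(X ≤ 15) at rate 0.0045 × (1 − m).

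| m (assumed) | Expected events missed | Chance of passing at a true 0.45% |
|---|---|---|
| 0 | 0 | 4.5% |
| 10% | 2.3 | 11% |
| 20% | 4.7 | 24% |
| 25% | 5.8 | 33% |

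**Step 4. Late events counted (illustration, upper bound).** Suppose every event in d extra days is counted and the hazard is constant. The rate becomes 0.0024 × (30 + d)/30.

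| d (assumed) | Expected extra events | Power |
|---|---|---|
| 0 | 0 | 81% |
| 1 | 0.4 | 78% |
| 3 | 1.2 | 70% |
| 5 | 2.1 | 62% |

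The last row needs every call to be made on day 35.

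**Step 5. Compare the descriptions of ascertainment.** Data collection speaks of VTE that is present. Study method speaks of symptoms suggesting that VTE has developed, sets no look-back period, and sends for imaging those who have symptoms. Any event first found through the call is imaged on or after day 30. The imaging date therefore cannot separate onset by day 30 from onset on days 31 to 35, and the article names no other date for the purpose.

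**The case against.** A reader might infer that the call is the only assessment, that earlier events are certain to be lost, that events after day 30 will be counted, and that no onset date is collected. The documents support none of these.

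- **Box 1 is not shown.** Its questions may cover the whole 30 days, ask about earlier diagnoses and record dates. One word in Data collection does not settle that.
- **Other sections are worded more widely.** Study method and Safety considerations both refer to symptoms of the development of VTE, which is not confined to the day of the call.
- **The call is not the only source.** Ethics and dissemination lists a 30-day morbidity audit beside the survey, and Safety considerations says the other data are already captured by the hospitals. Events in the treating hospital's records may be recovered this way.
- **The outcome definition excludes onset after day 30.** A call made after the window closes is needed to cover all 30 days.
- **An episode that settled without imaging never meets the stated outcome,** so it cannot be counted as a missed event.
- **The shares in Steps 3 and 4 are assumptions,** and the two errors pull in opposite directions.

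All of this stands, and it narrows the point. What remains is that two sections describe the same call differently. The narrower description conflicts with the outcome, and the design label agrees with the narrower one. The audit is mentioned once, to justify keeping identifiers, and is not tied to the primary outcome or to outside records. So no route is described for a VTE imaged at another hospital. This is a conflict between passages of the article, not merely detail left to a fuller document. A later analysis plan cannot easily recover diagnoses or dates that were never asked for.

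**Conclusion.** The point holds as an inconsistency to be corrected, not as proof of biased ascertainment. A cumulative outcome by day 30 is paired with a call described as finding VTE present on days 30 to 35, in a study labelled point prevalence. As described, a VTE imaged and treated elsewhere before the call can be missed, and an event with onset on days 31 to 35 may be counted.

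Its importance comes from the narrow decision margin of one event between passing (15) and failing (16) at n = 5190. With 10% of events missed, about 2.3 at a true 0.45%, the chance of wrongly passing would go from 4.5% to 11%. That figure rests on the exact one-sided rule and on a missed share that is not in the documents. The net effect of the two errors is unknown.

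This should be fixed, but the documents do not support calling it a fatal flaw.

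**What to change.** 1. **Study method and Data collection:** state that the call and the morbidity audit cover any VTE from surgery to day 30, including one already diagnosed or treated at any hospital. Obtain the imaging report for such events. Ask about symptoms at any time since surgery and record the onset date. If Box 1 already does this, align the text with it.
2. **Primary outcomes:** count an imaging-proven event if symptom onset was on or before day 30, whatever the imaging date. List events with later onset separately.
3. **Aims and objectives, and Study design:** replace the point-prevalence label with 30-day cumulative incidence.

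**Cost:** one or two questions and a date field in a call planned at 2 to 5 minutes, and occasional requests for outside imaging reports. The observed rate may be slightly higher. No extra patients are needed and the sample size stays at 5190.
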